### 2.5. Outcomes

#### 2.5.1. Primary Outcome

Hemodynamic evaluation will be performed using the PhysioFlow^®^ device (Manatec Inc., Paris, France). It is a non-invasive cardiac output monitor that provides hemodynamic parameters through transthoracic electrical bioimpedance signal analysis. PhysioFlow measures changes in impedance by applying a high-frequency alternating current (75 KHz) with low amplitude (3.8 mA) through the chest. Two sets of electrodes (PhysioFlow OS-50, Manatec Biomedical, Macheren, France)—one transmitting and the other receiving the electric current—will be applied above the supraclavicular fossa at the left base of the neck and along the spinal line at the thoracolumbar transition. An additional pair will be used for continuous electrocardiographic monitoring, recorded as recommended by the manufacturer after shaving and cleaning the skin with alcohol, followed by abrasion with Nuprep^®^ (Weaver and Company, Aurora, CO, USA) gel.

The sEMG is used to acquire and process respiratory muscle activity, a non-invasive technique performed with the BTS FreeEMG 1000 (Milan, Italy) device from BTS Bioengineering, which performs all amplification and filtering signal processing. The signal is acquired using 4 sensors connected to 4 disposable electrodes (4 cm long, 2.1 cm wide and 2 cm between poles) placed on each muscle to be analyzed after proper skin preparation according to the appropriate positioning in the literature for better signal acquisition. The skin preparation will be done by shaving, cleaning with 70% alcohol, rubbing the skin with gauze and applying the electrodes in the direction of the muscle fibers, according to the SENIAM recommendations (1999) [27]. The analyzed muscles are: sternocleidomastoid (SCM), scalene (ESC), parasternal (PARA) and rectus abdominis (RA), all on the right side, positioned as follows at the lower third of the distance between the mastoid process and the sternoclavicular joint [28]; 5 cm from the sternoclavicular joint and 2 cm above this point [29]; at the second intercostal space and 3 cm from the sternum at the umbilical line, 4 cm from the umbilicus [30]. The data are acquired and stored by the BTS FreeEMG 1000 (BTS Bioengineering), which handles all amplification and filtering of the signal acquired by the 4 sensors. The collected signals are stored using the SmartCapture software (BTS Bioengineering, Milan, Italy) and analyzed using the SmartAnalyzer program version 1.10.470.0.

The analysis of the myoelectric signal is performed using the Root Mean Square (RMS), which evaluates the amplitude of the signal in microvolts. For the normalization of the sEMG signals of the SCM and ESC muscles, the electromyographic values of the PImax maneuver will be analyzed, and for the PARA muscle, the MVV maneuvers, while the normalization of the RA muscle signal will be obtained from the Maximum Voluntary Isometric Contraction (MVIC) maneuver.

The recorded sEMG signals are pre-processed with a Butterworth bandpass filter from 20 to 400 Hz. To filter the cardiac signal, we will use a Butterworth high-pass filter of 20 Hz. The use of electromyographic signal processing techniques such as filtering, smoothing, and rectification will precede the calculation of the mean value, which will then be adjusted as %RMS according to the normalization for each subject.

#### 2.5.2. Secondary Outcomes

Anthropometric data (height, weight, BMI) and an initial assessment form including age, sex, marital status, occupation, smoking, alcohol use, medication use, sleep duration in hours per day, presence of chronic diseases, heart disease, lung disease, psychological or psychiatric diagnosis, and previous cannabis use, including oil, will be collected from all subjects.

The initial assessments will include a clinical evaluation, covering vital signs (temperature, pulse, blood pressure, respiration, and heart rate) as well as the Hamilton Anxiety Scale (HAM-A) (Hamilton M, 1959) [31] to assess the presence and severity of anxiety symptoms in participants. The HAM-A consists of 14 items, each defined by a set of symptoms that measure both psychological anxiety (restlessness and psychological distress) and somatic anxiety (physical complaints). Each item is scored on a scale from 0 (none) to 4 (severe), with a total score ranging from 0 to 56, with a score below 17 indicating mild anxiety, between 18 and 24 indicating moderate severity, and between 25 and 30 indicating moderate to severe anxiety [31].

The Borg scale and dyspnea are also used, along with other monitoring measures such as respiratory rate (RR), heart rate (HR), and peripheral oxygen saturation (SpO2), which are monitored and recorded every 2 min during the PRE-IN, IN, and POST-IN phases.

During spirometry, the following variables are evaluated: Forced vital capacity (FVC), forced expiratory volume in one second (FEV_1_), forced expiratory flow between 25% and 75% of the FVC curve (FEF_25–75%_), and FEV_1_/FVC ratio. The evaluation is considered complete when three acceptable curves have been performed with two reproducible results according to the American Thoracic Society (ATS) and European Respiratory Society (ERS) guidelines [32]. The equipment used is a KoKo DigiDoser^®^ digital spirometer (Longmont, CO, USA) connected to a computer with the device’s own software, and calibration is performed daily by injecting a volume of air with a 3-L calibration syringe. The best spirometric values are selected for analysis. The values obtained will be compared with the relative and absolute values for the Brazilian population [33].

Inspiratory and expiratory muscle strength will be assessed by maximum respiratory pressures (and PEmax, respectively). The measurement will be performed with the digital manometer MicroRPM^®^ (Micro Medical, Rochester, UK). Prior to each test, participants will be instructed in the procedures and the assessors will demonstrate how to perform the maneuver. Participants will perform a trial maneuver for learning purposes and the assessment will be considered complete when there is less than 10% variation between the two maximum values. The technical criteria for acceptability and reproducibility of the maximum airway pressure tests follow the ATS/ERS guidelines [34].

Tissue oxygenation is assessed by near-infrared spectroscopy (NIRS) using the NIRSPortamon^®^ device (Artinis Medical Systems, BV, Elst, The Netherlands). The technique is based on the application of light at a near-infrared wavelength, taking into account the absorption and scattering principles based on spatially resolved spectroscopy. The NIRSPortamon^®^ is a non-invasive, portable, wireless device with a receiver and three LEDs spaced 30, 35 and 40 mm apart that detect the absolute concentrations of oxyhemoglobin (O_2_Hb), deoxyhemoglobin (HHb), total hemoglobin (tHb) and oxygen index, blood volume and flow. The device uses wavelengths of 760 and 850 nm and the Tissue Saturation Index (TSI) in muscle tissue, providing information on local consumption. A Bluetooth connection allows online monitoring while the individual is performing activities and is not affected by the presence of equipment such as sEMG and sECG. The device is attached to the individual’s skin over the medial vastus muscle using adhesive tape after shaving and cleaning the area with 70% alcohol. Data analysis was performed using Oxysoft software version 4.0 (Portamon Artinis Medical Systems, BV, Elst, The Netherlands).

### 2.6. Monitoring and Adverse Effects

This study is a Phase 1 research project; therefore, no previous studies have reported serious adverse effects from the use of CBD or THC oil. Potential pharmacological effects will be monitored throughout the study, and in anticipation of reactions such as allergic reactions or exacerbated effects, the intervention will take place in a hospital setting with a multidisciplinary health care team. The investigators are committed to providing appropriate and prompt treatment for any adverse events that may occur during the study. In the case of serious adverse events or effects, a final decision will be made to discontinue the study. In case of psychiatric symptoms, the participant will be accompanied by a psychiatrist and will receive pharmacological treatment if necessary.

### 2.7. Statistical Analysis

Normality and distribution of data will be assessed using the Shapiro–Wilk test. For descriptive analysis, we will use mean and standard deviation for parametric data and median and interquartile range for nonparametric data. Intra- and inter-group comparisons will be made using mixed model analysis, specifically the Generalized Estimating Equations (GEE) test, with adjustment for multiple comparisons using the Sequential Bonferroni correction in IBM SPSS Statistics version 25 (International, based in Armonk, NY, USA). Sample characterization data will be analyzed using GraphPad Prism 8.0 (GraphPad Software Inc., San Diego, CA, USA) for graph construction. A significant level of *p* < 0.05 and a 95% confidence interval (CI) are used for all analyses.

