## 2. Materials and Methods

This is a randomized controlled crossover clinical trial with a 1:1:1 allocation ratio, double-blinded, which will be described according to the Consolidated Standards of Reporting Trials (CONSORT) criteria [21] where the checklist will be available in the online Supplementary Materials, and the protocol will follow the description suggested by the Standard Protocol Items Recommendations for Interventional Trials (SPIRIT) [22]. This study will be conducted at the Onofre Lopes University Hospital, of the Federal University of Rio Grande do Norte. The study was authorized by Brazilian Health Regulatory Agency (ANVISA) and was registered in the Brazilian Clinical Trials Registry—ReBEC, a public registry, under the trial registration number RBR-3jsvtbr, with the registration date of 30 April 2024.

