### 2.1. Sample Size and Allocation

The sample size will be determined after a pilot study with five subjects, considering the cardiac output (CO) values as the main variable in intra- and inter-group comparisons through mixed model analysis of the Generalized Estimating Equations (GEE) test. An alpha error of 0.05 with a two-sided distribution and a test power of 80% will be established. Recruitment will be done through convenience sampling, using direct invitations and advertising on social media, posters, flyers on Instagram and WhatsApp, targeting the general population.

Participants will be randomly assigned to a single group, which will undergo five different types of interventions: (1) CBD + THC intervention at 12.50 mg (CBD + THC/12.50 mg), (2) CBD + THC at 18.65 mg (CBD + THC/18.65 mg), (3) THC intervention at 12.50 mg (THC/12.50 mg), (4) THC at 18.65 mg (THC/18.65 mg), and (5) placebo intervention (IP). The order of interventions for each individual will be randomized using the https://www.sealedenvelope.com website for analysis (accessed on 4 September 2025).

To conduct the five research interventions, we will use three different oils. The first is an THC oil with a concentration of 2.50 mg/mL “Naternal Full Spectrum Delta 9 THC”, from (Naternal^®^, Morrisville, NC, USA). The second is a Cannabis oil containing 50 mg/mL CBD and 1.83 mg/mL THC “Lazarus Naturals High Potency Full Spectrum” from (Lazarus Naturals^®^, Seattle, DC, USA). The third, used in the placebo intervention (IP), is an MCT (Medium Chain Triglycerides) oil used as a base for diluting the full-spectrum Cannabis and THC oils, consisting of 70% fractionated coconut oil and 30% corn oil.

During the THC evaluations, the mL dosages will be determined based on the concentration of the product. Similarly, in the evaluations of the CBD + THC intervention, the THC and cannabis oils will be combined to achieve an equal ratio of CBD and THC for each specific dose. In the placebo intervention, all participants will receive a dose of 5.00 mL of MCT. The dosages and corresponding values are detailed in Table 1.

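### GEE is labelled a mixed model in both the analysis and sample-size sections; if it is run with uncorrected robust errors, the 5% level is not held at sizes plausible for this crossover

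*Protocol article*

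**What the plan says.** Section 2.7 (Statistical Analysis) names the only inferential method: "Intra- and inter-group comparisons will be made using mixed model analysis, specifically the Generalized Estimating Equations (GEE) test". It adds sequential Bonferroni adjustment and a 0.05 significance threshold, and states that "a 95% confidence interval (CI) are used for all analyses".

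Section 2.1 (Sample Size and Allocation) uses the same label when it sets the basis for the sample size, "considering the cardiac output (CO) values as the main variable in intra- and inter-group comparisons through mixed model analysis of the Generalized Estimating Equations (GEE)". On error rates it says: "An alpha error of 0.05 with a two-sided distribution and a test power of 80% will be established". No number of participants is given: "The sample size will be determined after a pilot study with five subjects".

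Section 2 describes the trial as a crossover, and Section 2.1 says that each participant receives five interventions. The article does not state the covariance estimator (robust or model-based), the working correlation or the reference distribution.

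**The concern.** GEE and a mixed model are different methods. GEE estimates population-averaged effects, has no random effects, and is commonly paired with a sandwich variance whose justification needs many independent clusters. A mixed model specifies the within-person covariance through random effects, and its tests can use finite-sample degrees of freedom. The two also handle incomplete data differently. A reader of Sections 2.1 and 2.7 cannot tell which one will produce the primary p-values or determine the sample size.

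The choice matters because in a crossover the clusters are the participants. Adding interventions or repeated measurements per person does not add clusters. With few participants the uncorrected sandwich variance is too small and too variable for a normal or chi-square reference. The two-sided 5% level and 95% intervals would then not be delivered, and sequential Bonferroni would operate on p-values that are already too small. The same standard errors could also enter the sample-size calculation after the pilot.

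**Working it through.** **What can be reproduced.** The article gives no sample size, effect size or standard deviation, so no sample size or power figure can be reproduced. The 0.05 level is set, not derived. The check is therefore how well that level is held, as a function of the number of participants N.

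**Inputs.** From the article: five interventions per participant, two-sided 0.05, 95% intervals, sequential Bonferroni. Assumptions: N, complete balanced data, normal errors, identity link, uncorrected sandwich variance, z or chi-square reference.

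**Plausible N.** For a paired contrast with standardized difference d (assumed), 80% power at unadjusted two-sided 5% needs N = ((1.96 + 0.842)/d)² = 7.85/d². This gives 8, 13, 32 and 50 for d = 1.0, 0.8, 0.5 and 0.4. At 5%/10 the same calculation gives 14, 21, 54 and 84.

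**Single contrast.** The estimate is the mean of the N within-person differences. The sandwich variance is Σ(dᵢ − d̄)²/N², which is (N − 1)/N times the usual s²/N. Comparing with 1.96 therefore rejects when |t| on N − 1 df exceeds 1.96·√((N − 1)/N). At N = 20 the threshold is 1.96·√(19/20) = 1.910, and P(|t₁₉| > 1.910) = 7.1%.

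**4-df intervention test.** The Wald statistic equals 4N/(N − 4) times an F variable on 4 and N − 4 df, so it rejects when F > 9.488·(N − 4)/(4N). At N = 20 the threshold is 9.488·16/80 = 1.898, and P(F₄,₁₆ > 1.898) = 16.0%.

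**Family-wise error.** Ten pairwise contrasts with sequential Bonferroni were simulated under the global null, with 20,000 trials per N.

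| N (assumed) | Single contrast | Coverage of 95% CI | 4-df test | Family-wise, 10 pairs |
|---|---|---|---|---|
| 10 | 9.6% | 90.4% | 33% | 19% |
| 20 | 7.1% | 92.9% | 16% | 9.7% |
| 30 | 6.4% | 93.6% | 11.6% | 7.5% |
| 40 | 6.0% | 94.0% | 9.7% | 6.6% |
| 60 | 5.7% | 94.3% | 7.9% | 5.3% |

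Coverage is 100% minus the single-contrast rejection rate. With a t reference and the usual variance, the simulated family-wise error was 3.8% to 4.4% for N from 8 to 60.

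**Period effects.** With period in the model (exchangeable working correlation, assumed ρ = 0.6, 3,000 trials), the rates rise to 12.8% for one contrast and 42% for the 4-df test at N = 10, and to 8.7% and 20% at N = 20. A within-subject analysis with t/F reference on the same data stayed at 4.5% to 5.6% and 4.3% to 5.8% for N from 8 to 60. Its errors had equal variances, so its own assumptions held exactly.

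**The same analysis under unequal variances.** Take assumed intervention SDs of 1, 1.5, 1.5, 2 and 2. The pooled variance averages (1 + 2.25 + 2.25 + 4 + 4)/5 = 2.7, whereas the two most variable interventions each have variance 4. For the contrast between those two, the effective threshold is about 1.96·√(2.7/4) = 1.61, a rejection rate near 10.7% in large samples. Simulation gave about 10% at N = 10, 20, 30 and 40, with no improvement as N grows. The sandwich gave 9.4% / 7.1% / 6.5% / 5.9%.

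**The case against.** The strongest objection is that the document fixes neither of the two things that drive the inflation. It states no sample size, and a five-person pilot does not make the main trial small. It also names no covariance estimator, and a condensed article may leave that detail, or a small-sample correction, to the full protocol or analysis plan. This stands: a reader might infer that the trial will certainly have false-positive rates well above 5%, and the document does not support that. Only the mislabelling is unconditional. Even there, the wording in Section 2.7 suggests that GEE is the procedure intended.

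Two further inferences are tempting and also unsupported. The first is that an intervention-by-stage test would be inflated even more, because it has more degrees of freedom. That presumes a full five-by-three table. Section 2.4 says that all interventions are evaluated in three stages, but it also places the PRE-IN assessment in the first morning session, for comparison with the later stages of the other interventions. On that second reading PRE-IN is one shared measurement and the full interaction cannot be estimated, so no figure is given for it here.

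The second is that any mixed model would hold 5%. The unequal-variance check shows otherwise: a pooled-variance analysis can be off by about as much, and more data do not cure it. Replacing GEE without attention to the covariance structure would trade one risk for another.

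The objection does not remove the double naming of the primary method. Nor does it change the fact that, at the sizes which large or moderate paired effects would imply, the uncorrected version of the named method misses the stated level.

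**Conclusion.** The point holds in conditional form and should be acted on. Without any assumption, Sections 2.1 and 2.7 both describe a marginal method as a mixed model, so the primary analysis and the basis for the sample size are not identified.

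Conditional on uncorrected sandwich errors, a z or chi-square reference and complete balanced data, the stated level is clearly missed at about 20 participants or fewer: at least 7% per contrast, 16% or more on the 4-df test, and about 10% or more family-wise over ten pairs. At 40 to 60 participants the single contrasts (5.7% to 6.0%) and the family-wise rate (5.3% to 6.6%) are close to nominal, and only the 4-df test remains materially inflated. The size of the problem therefore depends on a sample size that is still to be set.

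**What to change.** State one model, in the same words, in Sections 2.1 and 2.7. Either of these would serve:

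- **Linear mixed model (REML).** Participant as a random effect; fixed effects for intervention, stage, breathing condition and period; only those interactions that the PRE-IN schedule makes estimable; a covariance structure that allows unequal variances; Satterthwaite or similar degrees of freedom.
- **GEE retained.** A bias-corrected sandwich variance with a t/F reference, and the working correlation named.

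Base the post-pilot sample size on the model chosen. If uncorrected robust variances from the pilot were used instead, the expected variance of a contrast would be (5 − 1)/5 = 80% of the unbiased value, before allowing for the imprecision of five participants.

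The cost is an edit to both sections, and a check that the named software version offers the chosen option. The mixed model relies on approximately normal residuals and an adequate covariance structure. Both should be checked, with a log scale as a fallback if residuals are skewed. Because the sample size is still open, the change can be made before it affects anything else.

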## 3. Discussion

This will be a randomized, double-blind, controlled, crossover study to be conducted in a hospital setting, aiming to evaluate the acute effects of different doses of full-spectrum cannabis and THC oils on cardiovascular hemodynamics and respiratory muscles’ electrical activity in healthy subjects. The use of cannabis oil, especially in the form of full-spectrum extracts or THC, has attracted increasing interest in various health fields. Although most studies have focused on the effects of these compounds on the central nervous system [35,36] and specific neurological conditions [12,37,38], there is a gap in knowledge regarding their physiological effects on the cardiovascular and respiratory systems, as well as their tolerability and the recommended doses for acute effects.

Stanley [39] suggests, in a review, that administered CBD does not appear to have any effect on resting blood pressure or heart rate; however, it reduces the cardiovascular response to various types of stress. Thus, CBD treatment may play a protective role in reducing the effects of cardiac ischemia and reperfusion, or in mitigating cardiac dysfunction associated with diabetes. On the other hand, Jadoon et al. [40] observed that a single oral dose of CBD reduced resting blood pressure compared to the placebo group. These responses may be related to the pharmacokinetic variability of effects, as well as the different doses and routes of administration used.

Pickering et al. [41] evaluated 9 healthy individuals and individuals with COPD (Chronic Obstructive Pulmonary Disease) who were subjected to dyspnea induced by inhalation of different loads of carbon dioxide (CO_2_). The research participants underwent an evaluation with an intervention using an oromucosal cannabis spray containing 2.7 mg of THC and 2.5 mg of CBD, where the maximum dose was 4 sprays. Despite the small number of participants evaluated, the study demonstrated that cannabis may attenuate descriptors of dyspnea, potentially detecting an improvement in the unpleasantness of induced dyspnea when compared to the placebo group, especially in subjects with COPD. However, it is still necessary to better understand the physiological response of the drug in the cardiovascular and respiratory systems to effectively use it in the treatment of diseases and dysfunctions.

Changes in respiratory muscle activity can significantly affect lung capacity, leading to symptoms such as dyspnea, fatigue, and exercise intolerance. The results of this research could provide relevant scientific evidence on the effects of cannabis oils and THC at different doses on the respiratory muscular system, and this information may have important clinical implications, helping in the evaluation of risks and benefits associated with the use of these substances, as well as in the development of personalized therapeutic protocols for patients with specific respiratory conditions.

Seeking to better describe these pharmacological effects, Nitecka-Buchta et al. [42] evaluated the muscle relaxant aspects of cannabis through sEMG in the masseter muscle in a double-blind clinical trial. And observed that, when applied transdermally in the form of an ointment, cannabis reduced electrical activity and pain intensity, which was beneficial for the group with temporomandibular dysfunction. However, further studies are needed to assess the effects of oral cannabis use on the electrical activity of respiratory muscles and its influence on breathing.

Therefore, by investigating the effects of both oils at varying doses in the healthy population, it is possible to gain a more precise understanding of the direct impacts of these substances on cardiovascular hemodynamics and respiratory muscle electrical activity. Furthermore, it may provide important insights for other target populations, such as those with neurological, respiratory, or cardiac diseases. Additionally, this study aims to expand scientific knowledge and could serve as a foundation for future studies exploring the therapeutic potential of these substances in various health conditions, offering valuable information for clinical decision-making and contributing to the advancement of knowledge in this field.

